### Trial monitoring and management

This study is coordinated and managed by the Black Dog Institute, a mental health research institute affiliated with UNSW, Sydney, based in Sydney, NSW, Australia. All clinician support and clinician-administered measures will be delivered via telephone and email by research clinicians based at the Black Dog Institute.^1^ All study procedures and the collection of participant data, including consent and outcome measures, will be administered via the REDCap survey platform [54, 55], which is hosted on secure servers commissioned by UNSW at GovDC Data Centres located in Sydney, Australia. Participant data is de-identified: the REDCap platform automatically generates a unique participant code which the research team will use to refer to participants to protect their confidentiality; and identifiable applicant and participant data will only be accessible to members of the research team. The data generated from REDCap is stored in a SQL Server 2016 database which is backed up daily. There will be no data monitoring committee or planned interim analyses.

For analyses, study assessment data will be exported from the REDCap platform via a Microsoft Excel file to SPSS version 26. These files will be password protected and stored on UNSW OneDrive. No identifiable information (e.g. name, date of birth) will be included in the main datafile used for analysis. This dataset will be stored using a password protected OneDrive file.

### Safety monitoring and management

This trial will follow a standardised risk management protocol based on previous clinical trials of digital mental health interventions run by the research team and use a Trial Management Group (TMG) to supervise the overall conduct and safety of the trial. This is in accordance with the National Health and Medical Research Council (NHMRC) guidelines on Data Safety Monitoring [57], which state that a TMG is an appropriate alternative to a Data Safety Monitoring Group for non-commercial trials. All adverse events and serious adverse events will be formally recorded and reported to the TMG, and in a report and to the UNSW HREC by the chief investigator. The TMG may recommend pausing or ending the trial due to participant safety concerns. UNSW can audit trial conduct at any time, and this process will be independent of the investigators.

To ensure the safety and wellbeing of participants, several methods are incorporated into the study design. First, all applicants will complete measures of suicidal ideation and depression symptom severity (i.e. PHQ-9). Second, eligible applicants will also complete a comprehensive phone-based risk assessment with a study clinician during the enrolment telephone interview. Any applicant who has recent history of self-harm, active suicidal intent, or recent suicide attempts will be ineligible for the study, and complete a phone-based safety plan, and provided referrals to alternative sources of crisis and ongoing support. Any applicant or participant who endorses suicidal ideation (without current intent) will complete a collaborative phone-based safety plan prior to their initial or ongoing participation; this safety plan will be emailed to them. If needed, further support services accessible after the study will also be discussed with participants. Participants will be emailed crisis support options in their orientation email, instructed to monitor for mood changes during trial participation, and contact the research team or their GP during business hours for non-emergencies, or call the state-wide crisis support teams or emergency numbers if in crisis.

Third, all participants will be actively monitored for mood deterioration, increase in suicide risk, or the experience of adverse side effects of the intervention in their questionnaire responses (PHQ-9, pre-module questions), during clinician check-in calls, and during the follow-up questionnaires and interview. Automated alert emails will be sent to the trial coordinator if participants score greater than ‘1’ on item 9 of the PHQ-9 at any time during the trial, indicating experience of suicidal thoughts several times over the past 2 weeks, and participants will be contacted by a study clinician the same or next business day to check in and complete a risk assessment and safety plan as needed. Participants will be provided the option to withdraw from the study if it is causing distress and referral options for a higher step of care will be discussed. Any presence of risk or changes in applicant or participant risk profile will be discussed amongst the TMG during weekly meetings and documented in the trial safety monitoring register.

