### Eligibility criteria

Inclusion criteria includes adults aged 18 years or over, residing in Australia, fluency in written and spoken English, access to a computer and the internet, elevated scores on both the Social Interaction Anxiety Scale [> 34; SIAS, [52]] and the Social Phobia Scale [> 24; SPS, [52]], meeting DSM-5 diagnostic criteria for SAD according to a telephone diagnostic interview, willingness to provide basic demographic information and their general practitioner’s (GP) contact details, and on a stable dose of medications if applicable (no new medications or changes to existing medications in the 2 months prior to applying for the study).

Exclusion criteria are as follows: self-disclosed pre-existing diagnosis of schizophrenia, psychosis or bipolar disorder, daily or nearly daily suicidal ideation (score of ‘3’ on item 9 of the Patient Health Questionnaire-9 [PHQ-9; [53]]), or recent suicidality as determined by clinician interview (i.e. current suicidal intent, self-harm, or suicide attempts in the past 5 years), very severe depression (PHQ-9 scores of ‘24’ or above), currently receiving CBT, or commenced or changed mental health medication in the 2 months prior to application.

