### Control: waitlist control group

Participants allocated to the WLC group will be informed that they will be able to access the treatment after a waiting period of 6 weeks, during which they will complete three sets of online questionnaires. WLC participants will be sent automated emails via the REDCap platform with a link to complete questionnaires the day after their interview is completed (baseline, T1), 2 weeks later (T2), and 6 weeks post-baseline (T3). At T3, they will also be contacted to re-complete the telephone diagnostic interview, after which they will schedule the start date for their treatment week if they still choose to participate. WLC participants will follow the same procedure as the treatment group before (preparation call), and during their treatment week, receiving the treatment and clinician support over 1 week, and complete post-treatment questionnaires 1 week after completing their intervention. This post-treatment assessment will be used to assess WLC participants’ immediate treatment outcomes which will be included in the analysis of predictors of treatment outcome. The WLC will not be asked to complete any further follow-up assessments to minimise participant burden.

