### Clinician support

Scheduled check-in calls will follow a standardised script. Questions are designed to prompt discussion with the participant around their understanding of the content and skills covered in the preceding modules, their goals, practice of the skills, and assistance troubleshooting any barriers or challenges to skills practice (e.g. tailoring an exposure hierarchy to their personal goals). Participants can request to complete their check-in calls via email if they are unable to speak over the phone (e.g. phone calls are too anxiety-provoking) or require less intensive support. If participants require further support over the following days, they can request a check-in call on day 5 of the program. Participants are informed that they may email the research team at any time during the treatment week with questions or if they require technical or clinical assistance (and will be responded to within business hours). All contact hours with participants will be recorded by clinicians in the REDCap platform.

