### Additional outcome measures

Participants in the treatment group will be administered additional questionnaires to assess the acceptability, treatment satisfaction, treatment engagement, feasibility, and side effects of the intervention.

Module feedback: Prior to starting each lesson, participants will be asked to provide brief feedback about the previous module with the question ‘Do you have any feedback (positive or negative) about the previous lesson that you would like to share with us? Please be honest as it helps us to improve the program’.

Strategy use: Participants will be asked about the frequency with which they have used each strategy (e.g. ‘using video feedback’ or ‘thought challenging’; from 0 = never to 5 = very often), and an open-ended question asking which strategy they feel was most helpful in reducing their fear of social situations.

Treatment Satisfaction Questionnaire [TSQ; [88]]: the TSQ is a 5-item measure of treatment satisfaction used frequently in RCT studies evaluating CBT treatments [e.g. [89–91]]. It prompts participants to rate on a series of Likert scales their overall level of satisfaction with the treatment, the pace of the treatment, how logical it seemed, how confident they were that the program was successful in teaching them skills to manage their anxiety, and how confident they would be in recommending the treatment to a friend with similar symptoms.

Side effects: At post-treatment, participants will be asked to describe any positive effects or events and any unwanted side effects or negative events they feel occurred because of the program. Prior to starting each module, participants will also be asked if they experienced any difficult or adverse events since the last lesson.

Further open-ended questions will be included in post-treatment questionnaires regarding participants’ treatment experiences, including which aspects of the treatment they found most helpful and unhelpful and that they liked and disliked the most; how the program could be improved; how relatable they found the characters; how the characters could be improved to be more relatable to them; and any further comments.

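### The protocol requires a safety plan for any endorsed suicidal ideation, but the printed PHQ-9 item 9 alert starts above 1, so a new score of 1 triggers no prompt contact

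*Protocol article*

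**What the plan says.** All the main statements are in the protocol article, Safety monitoring and management.

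- **Duty.** Any applicant or "participant who endorses suicidal ideation (without current intent) will complete a collaborative phone-based safety plan prior to their initial or ongoing participation". No score or frequency limits this duty, and the reference to ongoing participation carries it past enrolment.
- **Alert.** "Automated alert emails will be sent to the trial coordinator if participants score greater than ‘1’ on item 9 of the PHQ-9", at any point in the trial. The article explains this score as "indicating experience of suicidal thoughts several times over the past 2 weeks". A study clinician then makes contact that day or the next business day, assesses risk, and completes a safety plan where needed.
- **General monitoring.** Participants are also monitored through their questionnaire responses (the PHQ-9 is named), check-in calls, and the follow-up questionnaires and interview. In addition, "Any presence of risk or changes in applicant or participant risk profile will be discussed amongst the TMG during weekly meetings and documented".

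The only item 9 score with a printed meaning is in Eligibility criteria, which excludes people with "daily or nearly daily suicidal ideation (score of ‘3’ on item 9 of the Patient Health Questionnaire-9".

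**The concern.** A safety duty that covers all ideation needs a route that picks up all ideation. The only numeric route printed starts above the lowest non-zero score. If the alert was built as printed, the promised safety plan for someone who newly scores 1 depends on a person noticing the response in an online questionnaire.

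The stake is participant safety and the accuracy of a published safety threshold that later trials of this programme might copy. Estimands, power, error rates and the efficacy analysis are not involved.

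**Working it through.** There is no figure in the plan to reproduce. The check is to run each item 9 score through both rules.

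**Inputs.** Item 9 takes whole scores up to 3, and 3 means daily or near-daily ideation (Eligibility criteria). *Assumption:* 0 means no ideation and 1 means some. The article does not print the anchors for 0, 1 or 2.

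| Item 9 score | Safety plan required by the duty? | Alert as printed (> 1)? | Alert at 1 or above? |
|---|---|---|---|
| 0 | No | No | No |
| 1 | Yes | **No** | Yes |
| 2 | Yes | Yes | Yes |
| 3 | Yes | Yes | Yes |

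The rules differ at one score, 1. Moving the trigger to 1 or above removes the difference.

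**Is a score of 1 picked up some other way?** Table 2 places the PHQ-9 at recruitment, T1, T2 and T3.

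- *T1.* Waitlist participants receive the baseline link the day after the enrolment interview. Intervention participants complete baseline on treatment day 1, when a check-in call is also scheduled. Clinician contact is close in both arms.
- *T3.* Both arms have the telephone diagnostic interview.
- *T2.* Neither arm has a scheduled call. In the intervention arm the calls belong to the treatment week: days 1 and 3, and if more support is wanted "they can request a check-in call on day 5 of the program". Waitlist participants receive the corresponding support only later: "WLC participants will follow the same procedure as the treatment group before (preparation call), and during their treatment week". The next scheduled clinician contact after T2 is the T3 interview, at 6 weeks against 2 weeks: 42 − 14 = 28 days later.
- *Adverse-event questions.* "Prior to starting each module, participants will also be asked if they experienced any difficult or adverse events since the last lesson". At post-treatment, the intervention arm is also asked about unwanted effects or negative events put down to the programme. That question falls at T2 and might bring out some cases, but it is narrower than a question on ideation and does not reach the waitlist arm at its T2.
- *Waitlist post-treatment questionnaire.* Table 2 does not list its contents. If it includes the PHQ-9, the same question arises there, with no later assessment planned.

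T2 is therefore the clearest point where a new score of 1 has no stated prompt contact.

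**Does the gloss settle the intended threshold?** Thoughts occurring several times in two weeks could describe a band that begins at 1. That would suit a threshold of 1 or more better than a band running from 2 up to near-daily. But this reading depends on anchors that the article does not print, so it only hints at a slip.

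**The case against.** The strongest reply is that the two statements do different jobs. One says who must have a safety plan and gives no deadline. The other says when an automatic, rapid escalation fires. A universal duty with a higher bar for urgent contact is an ordinary tiered scheme. The article says that PHQ-9 responses are actively monitored and that any presence of risk, whatever the score, goes to the weekly TMG meeting. Nothing says that the alert is the only path to a safety plan. Operational handling of low scores may also sit in the standardised risk management protocol that the article mentions but does not reproduce.

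Much of this stands. The tiered reading is possible, and general monitoring may well have caught a new score of 1. It does not remove the point. The article prints a duty covering all ideation and a trigger that stops short of it, and states no timing or action for an unalerted score. Weekly discussion deals with risk that someone has already identified. The issue is how two printed rules fit together, not detail left to another document.

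It also stands that the exposed group is narrow. Daily or near-daily ideation and recent suicidality are excluded at entry, and people with ideation at enrolment should already have a safety plan. Only low-level ideation that emerges during the trial is in question.

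A reader might go further and infer that participants with suicidal thoughts were left without follow-up, or that the threshold is plainly a misprint. The article supports neither. It reports no item 9 results and no missed contacts, and it does not show the REDCap setting.

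**Conclusion.** The mismatch is real but small. As printed, the alert and its rapid clinician contact do not cover an item 9 score of 1, although the safety-plan duty does. The conclusion rests on one assumption, that 0 means no ideation and 1 means some.

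Whether this is a wording slip, a tiered scheme or a gap cannot be decided from the article. The number of participants affected is unknown: the planned sample of 50 is an outer bound, and nothing in the article supports a rate within it. No efficacy result depends on it. This is a low-priority correction to a safety statement, worth making because it is specific and cheap.

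**What to change.** State the alert trigger as an item 9 score of 1 or above, so that it matches the safety-plan duty in the same section.

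Trial status reports that data collection finished by the end of July 2024, so new wording protects nobody in this trial. Two steps follow:

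1. Check which threshold was programmed in REDCap. If it was 1 or above, only the sentence needs correcting.
2. If it was above 1, list the scores of 1 that were new since enrolment, starting with T2 and, if it included the PHQ-9, the waitlist post-treatment questionnaire. Compare them with the trial safety monitoring register, and report any without recorded follow-up to the TMG.

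The cost is one look at a system setting, a one-phrase edit and, only in the second case, a short data query. Later use of the protocol would bring a few more clinician calls, which the safety-plan duty already promises.

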### Intervention: 7-day iCBT for social anxiety disorder group

The intervention program follows the THIS WAY UP iCBT program for social anxiety (available on www.thiswayup.org.au), using the intensive 1-week format introduced in the pilot trial [33] and described further in Table 1. Participants allocated to the intervention group (iCBT for SAD group) will be able to choose their preferred start date for the intervention as early as the week after the phone interview. To streamline tracking of participants and shared clinical care between research clinicians during business hours, participants are scheduled to begin their treatment on a Monday and end the following Sunday. A preparation call following a standardised script will be scheduled for the week prior to a participant’s treatment week, reiterating treatment week instructions, discussing their treatment goals, scheduling check-in calls for days 1 and 3, and answering any questions prior to commencement.

On the first day of the treatment week, participants will receive an automated email from the REDCap platform notifying them that their first module is available, with a written record of instructions for the coming week. Participants will complete baseline questionnaires prior to the first module. Each day participants are instructed to spend 20–30 min reading module content, before downloading a brief summary and activity plan, and spending 3–4 h over the remaining day practising the assigned skills.

Following treatment completion, participants will receive an automated email via REDCap with a link to complete post-treatment (T2) and follow-up (T3) questionnaires. At 6 weeks (T3), participants will complete the telephone diagnostic interview (SAD and MDD modules).

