## Methods

### Trial design and setting

This superiority trial will utilise a two-arm, parallel group RCT design with an equal allocation ratio. Outcome measures will be assessed at baseline, post-intervention (primary endpoint, measured at 2 weeks post-baseline), and follow-up (secondary endpoint, measured at 6 weeks post-baseline). The primary time point of interest is post-treatment (2 weeks post-baseline). A 6-week follow-up was selected to ensure participants in the control condition were provided with the intervention after a reasonable duration and to reduce participant attrition.

This clinical trial is sponsored by the University of New South Wales (UNSW) and ethics approval has been granted by the UNSW Human Research Ethics Committee (HREC; HC#220,089). The trial has been registered with the Australian New Zealand Clinical Trials Registry on March 1, 2022 (ACTRN12622000361707).

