### Randomisation and allocation procedures

At the completion of the telephone recruitment interview, participants will be randomised to either the iCBT for SAD group or WLC group using a 1:1 allocation ratio. Allocation numbers will be determined by a person who is completely independent of the research team, using the random.org random number generator and stored in opaque sealed envelopes, only opened by the study clinician once an offer of participation is made.

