### Trial outcomes and description of materials

After randomisation, all participants will complete a set of self-report questionnaires at baseline (T1), post-treatment (T2), and at 1-month follow-up (T3). Both groups will also be asked to complete a brief phone diagnostic interview [the ADIS MDD and SAD modules; [56]] at the 1-month follow-up (T3). Table 2 includes a list of assessment measures used and at which time point.

**Table 2 Tab2:** Materials used at each study time point

Questionnaire	Recruitment (T0)	Baseline (T1)	Post-treatment (T2)	One-month follow-up (T3)
Demographics	X			
Eligibility questions	X			
ADIS-5 modules	X			X
SPS	X	X	X	X
SIAS	X	X	X	X
PHQ-9	X	X	X	X
WSAS	X	X	X	X
LPFS-BF 2.0		X		X
PID-5-BF		X		X
HSU	X			
CEQ		X		
TSQ^a^			X	
Strategy use			X	X

^a^TSQ is completed by the treatment group only

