### Statistical analysis

All analyses will be undertaken using intention-to-treat approach. Linear mixed models, with a random intercept for subject will be used to analyse primary and secondary outcomes, and covariances matrixes used to assess relationships between variables. This approach will be used to manage missing data and account for correlation between repeated measures. Before conducting the analyses, patterns of missing data will be assessed through data visualisation, and Little’s Missing Completely at Random (MCAR) test to determine whether the data are missing at random. If there are significant group differences (as determined by independent samples *t*-tests) in the amount of time elapsed between the intake interview and completion of baseline measures, this variable will be included as a covariate in the linear mixed models. Planned contrasts will be used to compare pre- and post-treatment, and pre-treatment and 1-month follow-up, and planned pairwise comparisons will be used to compare between-groups at post-treatment and follow-up. To control for the risk of type 1 error with a co-primary outcome, the alpha level for significance will be adjusted using a Bonferroni correction (alpha set at 0.025 to determine statistical significance for the SIAS and SPS co-primary outcome measures). Linear mixed models will be utilised to test the predictors of treatment outcome. Within- and between-group effect sizes will be calculated using Hedges’ *g* (with 95% confidence intervals) to estimate the within-group changes from baseline to post-treatment, and baseline to follow-up, and between-group differences on primary and secondary outcome measures at post-treatment and follow-up.

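### iCBT questionnaires depend on starting and finishing treatment, waitlist questionnaires run from the interview, so iCBT non-starters can be lost to the intention-to-treat model

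*Protocol article*

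**What the plan says.** All places are in the Protocol article.

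- **Randomisation.** "At the completion of the telephone recruitment interview, participants will be randomised to either the iCBT for SAD group or WLC group" (Randomisation and allocation procedures). T1 comes later in both arms: "After randomisation, all participants will complete a set of self-report questionnaires at baseline (T1), post-treatment (T2), and at 1-month follow-up (T3" (Trial outcomes and description of materials).
- **Waitlist arm.** Links are sent "the day after their interview is completed (baseline, T1), 2 weeks later (T2), and 6 weeks post-baseline (T3" (Control: waitlist control group). No treatment step is involved.
- **iCBT arm.** Participants "will be able to choose their preferred start date for the intervention as early as the week after the phone interview"; no latest date is given, and a preparation call comes first. "Participants will complete baseline questionnaires prior to the first module". Then: "Following treatment completion, participants will receive an automated email via REDCap with a link to complete post-treatment (T2) and follow-up (T3) questionnaires" (all in Intervention: 7-day iCBT for social anxiety disorder group).
- **Endpoint.** "The primary time point of interest is post-treatment (2 weeks post-baseline" (Trial design and setting), so it is dated from T1 and not from randomisation.
- **Analysis.** "All analyses will be undertaken using intention-to-treat approach" (Statistical analysis). The outcomes go into a random-intercept mixed model, which is also given the job of handling missing data.
- **Pre-randomisation scores.** SIAS and SPS are taken from every applicant at T0 (Trial recruitment processes; Table 2). The analysis text gives T0 no role.

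**The concern.** Outcome collection is tied to treatment uptake in one arm and to the calendar in the other. A person randomised to iCBT who withdraws before the treatment week has no T1, and T2 and T3, counted from T1, have no anchor. Under the literal wording of the T2/T3 trigger, a person who starts but does not finish has T1 and is never sent the primary-endpoint questionnaire.

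A mixed model copes with a missing visit by using the person's other visits. It takes nothing from a person with none. Nor does the conditional covariate for the interval from interview to baseline help: it deals with unequal delay and is undefined for anyone without T1.

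Not starting an intensive exposure programme may well be related to outcome. If such people drop out of the iCBT data while their counterparts in the waitlist arm stay in, the comparison is no longer between the groups as randomised, yet it would be reported as intention-to-treat.

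**Working it through.** **1. The plan's own figure.** Sample size calculations gives an effect of 0.92, alpha 0.05, power 0.80 and 20 per group, plus 5 for attrition. A two-sided two-sample t test needs 19.55 per group, rounded up to 20; 20/(1 − 0.20) = 25. Both reproduce. The attrition allowance is 5/25 = 20%; the article does not split it by timing.

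**2. Assumptions.** The documents give no number of non-starters. In the pilot 15 of 16 completed all modules (Background, 7-day iCBT for social anxiety disorder), so at most 1 of those 16 never started. Scaled to this trial, 25 × 1/16 = 1.6, hence 1–2 of 25. The article does not say whether the 16 include people who withdrew before starting. The upper case is 5 of 25. The effect of 0.92 is taken, by assumption, as the effect in starters.

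**3. Formula.** Let p be the share of the iCBT arm that never starts, δ the effect in starters, and g how much worse (in SD) non-starters' untreated outcome is than starters'. By randomisation the waitlist arm holds the same expected share of would-be non-starters.

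- Effect in all randomised, with no gain in non-starters: (1 − p)δ
- Starters against the whole waitlist arm: δ + pg
- Bias: δ + pg − (1 − p)δ = p(δ + g)

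**4. Results for δ = 0.92.**

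| Non-starters of 25 | p | All-randomised effect | Bias, g = 0 | Bias, g = +0.5 | Bias, g = −0.5 |
|---|---|---|---|---|---|
| 1 | 0.04 | 0.883 | 0.037 | 0.057 | 0.017 |
| 2 | 0.08 | 0.846 | 0.074 | 0.114 | 0.034 |
| 5 | 0.20 | 0.736 | 0.184 | 0.284 | 0.084 |

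At g = 0 the starters-only estimate stays at 0.92, which is 4%, 9% or 25% above the all-randomised effect. The bias vanishes at g = −0.92. With δ = 0 it is pg, so its sign follows g.

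**5. Check with the stated kind of model.** A random-intercept mixed model was simulated with 25 per arm, three visits, an assumed within-person correlation of 0.6, δ = 0.92, g = 0 and 200 runs per case. The contrast is the group difference in change from baseline to T2.

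| Non-starters | Everyone followed | No rows for iCBT non-starters | Only a baseline row kept for them |
|---|---|---|---|
| 5 of 25 | 0.75 | 0.93 | 0.93 |
| 2 of 25 | 0.82 | 0.90 | 0.90 |

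These agree with the closed form within simulation error: the SD of one run's contrast is √(2 × 0.8/25) = 0.25, so a mean of 200 runs has a standard error near 0.02. With δ = 0 and 5 non-starters, absent rows gave 0.02 at g = 0 and 0.09 at g = +0.5 (closed form 0.10).

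**6. What a baseline row alone does.** The last column shows that a T0 record without outcomes does not remove the bias, because the model then predicts for that person as if they had been treated. The same holds for a non-completer who has T1 but no T2 and gained nothing. If such a person gained an amount h, the bias becomes p(δ − h + g), which is smaller.

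**The case against.** A reader might infer that the plan removes non-starters from the iCBT arm and so overstates the effect, by as much as 25%. The article does not support that, for these reasons.

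- **No exclusion rule is written.** Intention-to-treat is declared, and the outcomes section intends all participants to complete T1 to T3. This stands. The loss follows from the stated triggers, which give non-starters no route to that intention.
- **A baseline of a kind exists for everyone.** SIAS and SPS are held at T0. Someone who answers T1 but never opens module 1 has a T1, and anyone who booked a treatment week has a planned Monday. This stands: what can be missing is T1 and a triggered T2/T3, not all baseline information.
- **The waitlist arm can lose people too.** Its participants also get T1 after allocation and may not return it. This stands. Only the loss tied to treatment uptake is confined to one arm.
- **Direction and size are conditional.** With no non-starters there is no bias, and with no true effect the sign is open. The 25% figure needs the whole attrition allowance to be non-starters with no gain. This stands.
- **Analysis sets and sensitivity analyses are commonly left to a statistical analysis plan that is not shown.** True, and their absence is not the point. The point is that the schedule as stated ties outcome collection to uptake in one arm, which a mixed model cannot repair.

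**Conclusion.** The point holds in a limited form, as a cheap improvement. The two arms are assessed on different triggers, and people randomised to iCBT who never start (read literally, also those who do not finish) can lack the T1–T3 data that the intention-to-treat model uses.

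If such people exist and the true effect is near 0.92, the estimate probably favours iCBT. The likely size is about 0.04–0.07 SD, assuming 1–2 non-starters of 25, no gain in them, and untreated outcomes like those of starters. The upper case on the same assumptions is 0.18 SD. The direction would reverse only if non-starters' untreated outcome were more than 0.92 SD better than that of starters. With no true effect, the bias could take either sign.

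**What to change.** Recruitment and data collection are closed and analysis is underway (Trial status), so re-dating T2 and T3 cannot create missing outcomes. The changes below use data already held.

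1. State that the analysis set is everyone randomised, with T0 SIAS/SPS as the baseline record for anyone without T1.
2. Report, by arm, how many people have no T1 and how many have no T2. If none are missing in the iCBT arm, the concern closes there.
3. Add a sensitivity analysis that imputes missing iCBT T2 and T3 values for non-starters and non-completers from the waitlist arm, given T0. This step addresses the bias; step 1 alone does not.
4. If the main model stays on T1–T3 only, describe it as an analysis of those with T1–T3 data rather than as intention-to-treat.

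The cost is an analysis-set statement, two counts per arm and one extra analysis. The downside is possibly a slightly smaller reported effect.
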